#### Smartphone and CuePD.

CuePD will be installed on an Apple iPhone XS (177g, 143.6 × 70.9 × 7.7 mm), which has embedded tri-axial accelerometer and gyroscope inertial sensors, sampling data at ±8 g and 100 Hz. The smartphone will be securely attached to the participants’ lower back at the 5th lumbar vertebra (L5) using a belt strap and phone holder. The app, built in React Native with JavaScript, uses the API ‘react-native-sensors’ to capture tri-axial accelerometer data at a frequency of 100 Hz, providing high-resolution motion data. It includes a countdown for data recording, initiated by a user prompt, and after each one-minute session, it transmits the data to a Python server on Azure through a RESTful API using HTTP POST requests. This server, deployed on an Azure virtual machine running Ubuntu 20.04, utilises Flask to handle incoming requests and process the gait characteristics using NumPy [48], SciPy [49], and PyWavelets [50] libraries for signal processing. The processed data is stored in a PostgreSQL database hosted on Azure, ensuring reliable data management and retrieval. The server then sends the calculated gait characteristics back to the phone through the same RESTful API.

All audio files for each cueing mechanism are stored as. MP3 files and hosted on Azure Blob Storage, ensuring scalability and durability. When the user initiates cueing on the app, the server retrieves the audio files and estimates the beat per minute (BPM) of the audio file using Librosa, an audio signal analysis library in Python [51]. The server then adjusts the tempo of the audio using the FFmpeg Python library, which provides a reliable time-stretching algorithm [52]. This adjustment aligns the music's beats-per-minute with the user's steps-per-minute (SPM) plus an additional 10%, which has been found effective in promoting longer strides, increasing gait speed, and reducing variability [53–59]. The processed audio file is then re-encoded as. MP3, saved back to the Azure Blob Storage and then sent to CuePD for playback. All participants will wear headphones, cleaned between participants, and comfortably placed on their head over their ears to listen to cueing modalities. For more details on CuePD, read here [60–62].

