
After completion of all walks, participants will complete:

(viii)**Goldsmiths Musical Sophistication Index (Gold-MSI)**: A 39-item (scored from 1 to 7) self-report designed to assess musicality across five subscales: active engagement (AE), perceptual abilities (PA), musical training (MT), singing abilities (SA), and emotional response (ER) to music [70]. This tool evaluates and provides the detailed extent and nature of musical experiences and skills, but also provides a broader score on musicality, General Music Sophistication (GMS), ranging from 32 to 126. For this study, the scale will be used to assess if there was a relationship between an individual’s general music sophistication and their adherence to the beat of the music cues. Furthermore, the relationship between an individual’s subscale results and beat adherence will also be assessed.(ix)**System Usability Scale (SUS):** This will evaluate perceptions of the app’s usability, complexity, and overall satisfaction [71]. The SUS produces a composite score that ranges from 0 to 100, calculated by first adjusting the responses from a set of ten questions. For odd-numbered questions, the process involves subtracting one from each score, whereas for even-numbered questions, the score is subtracted from five, resulting in adjusted values that fall between 0 and 4. These adjusted values are subsequently summed together, and the total is multiplied by 2.5 to derive the final SUS score, with higher scores reflecting superior usability.(x)**Cueing preference:** Lastly, participants are asked a question to determine preferred cueing modality, “Which cueing do you prefer, was it metronome, instrumental music or vocal music?”

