### Statistical analysis

For the first primary objective, all gait characteristics derived from CuePD and reference will be compared using ICC_2,1_ (absolute agreement), a two-way random-effects model for single measures that evaluate the absolute agreement between raters. The level of agreement will be interpreted as: < 0.5 shows poor agreement, 0.5–0.75 moderate, 0.75–0.9 good and 0.9–1.0 excellent. PCC’s will be calculated to measure the linear correlation between the two sets of results. Correlation coefficients will be interpreted as follows: zero (0), weak (±0.1 to ±0.3), moderate (±0.4 to ±0.6), strong (±0.7 to ±0.9), and excellent/perfect (+1 or −1).

The median, mean, standard deviation (SD), minimum/min, maximum/max, and standardised response mean (SRM) of cadence, stride length, gait speed and CV_stride-time_ will be calculated. These descriptive statistics will provide context for interpreting changes and help to clarify the magnitude and consistency of cueing effects. SRM allows for assessment of responsiveness and comparison of results to other studies. The SRM will be interpreted as: > 0.8 large positive response, 0.5–0.8 moderate responsiveness, and <0.5 low responsiveness where positive values imply an improvement for cadence, gait speed and stride length but negative is an improvement for CV_stride-time_, i.e., reduces variability.

To evaluate the cueing modality adherence, the percentage change in cadence from the baseline walk to each cueing modality will be calculated for each participant. The most effective cueing modality will be identified as the one producing a change closest to 10%.

Model assumptions will be formally checked, where residual normality and normality of gait characteristics within each cue condition will be assessed using the Shapiro-Wilk test, and sphericity with Mauchly’s test. The Greenhouse-Geisser correction will be applied if sphericity is violated.

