To evaluate the relationship between musical sophistication and response to cueing, two sets of analyses will be conducted using Gold-MSI subscale scores. Assumption checks, including the Shapiro-Wilk test and Q-Q plot inspections, will be used to assess the distribution of change scores prior to both analyses. First, the association between Gold-MSI scores and cue adherence (defined as the absolute deviation from a + 10% target increase in cadence) will be assessed using Spearman’s rank correlation coefficient, with Bonferroni correction for multiple comparisons across subscales. Second, associations between Gold-MSI scores and gait outcome improvements (percentage change in gait speed and stride length, and log-ratio change in ${\text{CV}}_{\text{stride}-\text{time}}$) will also be tested using Spearman’s correlation, with Bonferroni correction.

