### Exploratory objectives: preference, usability, and musicality

Exploratory objectives of the protocol also focus on the user experience and the clinical efficacy of the personalised auditory cues provided by CuePD. A significant part of this exploration involves understanding the preferences of PwPD for engaging with personalised music cues during routine walking exercises, compared to traditional metronome cues which are often perceived as monotonous and less engaging. This preference for music could play a crucial role in enhancing patient engagement and adherence to the rehabilitation process. Finally, the study explores how well patients’ musicality correlates with their ability to synchronise with the auditory cues. If no relationship is found, this would indicate that the success of music cueing-based interventions does not depend on a patient's inherent musical skills, potentially broadening the applicability of such treatments to a wider demographic of PwPD.

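### The Gold-MSI correlation scores adherence against a nominal +10% cadence change, so any error in the software-estimated music tempo would count as participant non-adherence

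*Protocol article*

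**What the plan says.** The construct is following the beat. The Gold-MSI item under Data collection aims to relate "general music sophistication and their adherence to the beat of the music cues". In Walking/gait tasks, each cued walk carries the instruction to walk to the beat. The Discussion (Exploratory objectives) asks how well musicality "correlates with their ability to synchronise with the auditory cues".

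The scores are built on cadence change from the baseline walk. Under Statistical analysis, "To evaluate the cueing modality adherence, the percentage change in cadence from the baseline walk to each cueing modality will be calculated" for each participant, and then "The most effective cueing modality will be identified as the one producing a change closest to 10" per cent. For the Gold-MSI correlation, adherence is "defined as the absolute deviation from a + 10% target increase in cadence". The binary rule (Adherence to cues and musicality) calls a rise of at least 5% adherent. None of these scores uses the tempo that was actually played.

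The tempo is produced in software. Under Smartphone and CuePD, "the server retrieves the audio files and estimates the beat per minute (BPM) of the audio file using Librosa", and the file is then time-stretched to the walker's step rate "plus an additional 10%, which has been found effective in promoting longer strides".

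**The concern.** Distance from the beat and distance from +10% are the same quantity only when the delivered tempo is exactly 110% of baseline cadence. If the estimate for a track is off, a participant who follows the music perfectly misses +10%, and the score records a device error as a failure to adhere.

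Tracks come from a study-supplied selection, so such an error would belong to the track and be shared by everyone who chose it.

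Two results could be touched:

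- **Gold-MSI correlation.** Tempo error unrelated to musicality is noise in the adherence score and weakens the correlation. This matters because the Discussion says in advance how a null will be read: "If no relationship is found, this would indicate that the success of music cueing-based interventions does not depend on a" patient's musical skill. Attenuation works in favour of that reading.
- **Modality ranking.** A modality could be marked down because its audio was mis-set, and nothing in the planned output would show this.

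**Working it through.** **Inputs from the article.** Intended tempo: 1.10 × baseline cadence. Adherence score: absolute difference between percentage cadence change and 10. Binary cut: 5%. Evaluable sample: about 55 (Sample size). Gold-MSI subscales: five, with Bonferroni correction. Significance level for secondary analyses: 0.05, so 0.05/5 = 0.01 per subscale.

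**Not in the article, so assumed and shown as ranges.** The relative error e of the tempo estimate, the spread of walkers around the beat, and the true correlation.

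**Step 1: what a perfect follower shows.** Let a track have true tempo T and estimated tempo T(1+e), and let baseline cadence be C. The stretch factor is 1.10C / [T(1+e)], so the delivered beat is 1.10C/(1+e). A walker exactly on the beat shows a change of 1.10/(1+e) − 1.

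- e = 0: +10.0%, the plan's own figure
- e = +0.5%: 1.10/1.005 − 1 = +9.5%
- e = +1%: 1.10/1.01 − 1 = +8.9%
- e = +2%: 1.10/1.02 − 1 = +7.8%
- e = +3%: 1.10/1.03 − 1 = +6.8%
- e = −2%: 1.10/0.98 − 1 = +12.2%

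Scored against the delivered beat, this walker is 0% off in every row.

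**Step 2: power of the Gold-MSI correlation.** Simulation with n = 55, two-sided level 0.01, true Spearman correlation −0.43 (Gaussian copula, 0.45), absolute tracking error half-normal with the scale shown, direction of error symmetric, and normal tempo error. With one error-bearing score per person, power (%) is:

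| Tracking scale | Tempo SD 0 | 0.5% | 1% | 2% | 3% |
|---|---|---|---|---|---|
| 3% | 76 | 71 | 55 | 22 | 9 |
| 5% | 77 | 74 | 67 | 46 | 27 |
| 8% | 77 | 76 | 73 | 61 | 49 |

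Sharing the errors within a 10-track library moves these by about 2 points at most.

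Each participant has three cued walks, and the article does not say whether the score is per cue or averaged. If the absolute deviation is averaged, power at tempo SD 2% and 3% is:

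| Tracking scale | Three cues, metronome exact | Two music cues only |
|---|---|---|
| 3% | 57 and 41 | 34 and 15 |
| 5% | 69 and 62 | 58 and 41 |
| 8% | 73 and 69 | 68 and 59 |

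Repeat runs agree within about 3 points. The severe losses therefore need tight tracking, a tempo SD of 2–3%, and scores that are not averaged over all three cues.

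**Step 3: the ranking.** Take a music cue with e = +2%, followed perfectly: +7.8%. Take an exact metronome with the walker 1% behind: 1.10 × 0.99 − 1 = +8.9%. The rule prefers the metronome, although the music was followed better (0% against 1% off the beat).

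**Step 4: the 5% rule.** A perfect follower drops below 5% only when e exceeds 1.10/1.05 − 1 = 4.76%. A walker 3% behind the beat drops below it at e above 1.10 × 0.97/1.05 − 1 = 1.62%. This rule is less sensitive, but not immune.

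**The case against.** The strongest reply is that the plan is consistent on its own terms. It sets the beat at +10% of baseline, so walking to the beat is a +10% change, and no passage says that the delivered tempo differs. The CuePD papers cited for detail may document tempo accuracy. This stands, and it rules out the stronger reading that a reader might infer: that tempos were mis-set, or that the musicality analysis is known to be badly underpowered. The documents support neither. What survives is narrower. The written score is right only if the tempo is exact, whereas a score against a checked tempo is right either way.

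Second, +10% is the therapeutic target, and the ranking sentence speaks of the most effective modality, not the best-followed one. A cue that plays too slowly does fall short of that target. This also stands, so the ranking should not be replaced.

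Third, the article already limits the weight of these results. The Discussion says that gait responses will not be read as definitive evidence that one cue is superior, and it treats musicality as exploratory. A second planned correlation, of Gold-MSI with gait speed, stride length and stride-time variability, does not use the +10% target.

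Fourth, cadence over delivered tempo is still tempo matching over one minute. It does not measure step-to-beat synchronisation. That is true, and the fix does not claim to.

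**Conclusion.** The point holds in a limited form. The Gold-MSI correlation scores adherence against a nominal target although the stated construct is adherence to the beat, and the two agree only if the software tempo estimate is exact. Any discrepancy is counted against the participant and would attenuate a correlation whose null result the article plans to interpret.

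The size is unknown. At zero error nothing changes. Under the assumptions above, power stays close to 77% at a tempo SD of 0.5% with moderate or wide tracking error. It falls to about 9% only in the worst corner of a model with one score per person. Averaging over three cues with an exact metronome keeps it at about 41% or more over the range tried.

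A reader might also infer that the gait-speed comparisons and the mixed ANOVA are compromised. They do not use the +10% target, so this scoring problem does not reach them. Mis-set audio could change how people walked, but those analyses would then report a real response to what was played.

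Grade: minor, a cheap improvement to a secondary or exploratory analysis.

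**What to change.** 1. Check the true tempo of each library track, or of each saved rendered file, once and independently of the Librosa estimate. Where the estimate doubled or halved the tempo, use the beat level that participants step to.
2. Tabulate delivered tempo by modality as a percentage of Walk 1 cadence.
3. In the Gold-MSI adherence correlation, score the absolute deviation of cued cadence from delivered tempo, and report the nominal +10% version alongside. State whether scores are per cue or averaged.
4. Keep the closest-to-10% ranking as the therapeutic-target measure, and report signed cadence relative to delivered tempo beside it, so that a mis-set tempo is visible.
5. Keep the 5% rule. At most, add a sensitivity version: adherent if cadence is at least 1.05/1.10 = 95.5% of delivered tempo.
6. Leave the mixed ANOVA and the gait-speed comparisons as written.

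The cost is modest analyst time and a second adherence measure to explain if the two disagree. Rebuilding any overwritten file depends on a record of each participant's track. Where that is missing, report how many and restrict the delivered-tempo version to the rest. No extra visits, participants or devices are needed, and the tempo played does not change.

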A two-way mixed ANOVA will be used to assesses the effects of cueing modality and walk order on outcomes, i.e., cadence, gait speed, stride length, and CV_stride-time_. Comparable to the referenced PD study, cueing modality will be modelled as a within-subject factor, while walk order as a between-subject factor to account for potential sequence effects. For each outcome, within-participant changes from baseline will be calculated using cue-specific difference scores. To account for differences in scale and statistical distribution among the outcomes, change scores will be computed using Equations (30)-(31):

Percentage change of gait speed and stride length from baseline, calculated as:

$$\%\Delta =\frac{\text{Cue Value}-\text{Baseline Value}}{\text{Baseline Value}}\times \text{1}\text{0}\text{0}$$
(30)

In contrast,${\text{ CV}}_{\text{stride}-\text{time}}$, a dimensionless ratio-based variable that may have a skewed distribution, change will be computed using the natural log-ratio of cue value to baseline:

$$\Delta_{log}=\text{log}\left(\text{Cue Value}+\in \right)-\text{log}\left(\text{Baseline Value}+\in \right)$$
(31)

where 𝜖 is a small constant to avoid the logarithm of zero. This transformation was chosen as ${\text{CV}}_{\text{stride}-\text{time}}$ is a ratio-based measure that can be highly skewed and exhibit unequal variances across conditions. Applying the *log* transformation to change scores helps to normalise the distribution and stabilise the variance, thereby supporting more reliable statistical comparisons of cueing effects on ${\text{CV}}_{\text{stride}-\text{time}}$ in this within-subjects design. Post-hoc comparisons between cueing modalities will be conducted using paired t-tests, with Bonferroni correction applied to account for multiple comparisons. Effect sizes will be reported using Cohen’s d.

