If assumptions for normality are not met, a Friedman test will be used to assess within-subject differences across cueing conditions. Post-hoc Wilcoxon signed-rank tests, with Bonferroni correction, will be conducted only if the Friedman test is statistically significant. For between-subject effects (e.g., walk order), where normality assumptions are violated, the Kruskal–Wallis test will be used to assess group-level differences between walk-order groups. Interaction effects between cueing and walk order will be explored non-parametrically by conducting separate Friedman tests within each walk order group. Effect sizes for non-parametric tests will be calculated using the rank-biserial correlation coefficient, $\text{r}=\text{Z}/\sqrt{\text{N}}$, providing a measure of the magnitude of the effects observed.

For the three primary comparisons, we will control the familywise error rate using a Bonferroni adjustment. Given three cueing modalities, statistical significance (*p*) will be evaluated at a two-sided α = 0.01/3 = 0.0033. Effect sizes (i.e., SRM) and 95% confidence intervals will also be reported. Secondary and exploratory analyses (e.g., comparing cueing modalities to one another, examining washout effects, assessing stride-to-stride variability) will not be subject to multiplicity correction. For these analyses, a two-sided *p*-value of 0.05 will be considered statistically significant across all parametric and nonparametric tests.

To assess whether the first cue produced short-term residual effects, we will calculate changes in gait outcomes from baseline to each cued walk and from each cued walk to its subsequent washout walk (WO1 and WO2). For each cue exposure, a carryover score will be calculated as the difference between the change induced by the cue and the change observed during the corresponding washout period, reflecting retained cue effects. The approach enables an evaluation of carryover effects after each cued walk separately, thereby capturing any cumulative or progressive retention of cueing effects. Group differences based on initial cue type (i.e., counterbalanced sequence) will be evaluated using one-way ANOVA or the Kruskal–Wallis test, depending on normality assumptions [74–80].

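### Shapiro–Wilk results decide, outcome by outcome, whether the joint cue-by-walk-order ANOVA gives way to rank tests, and the rank route's interaction check cannot test an interaction

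*Protocol article*

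**What the plan says.** All of this is in the Statistical analysis section of the protocol article.

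- **Default.** "A two-way mixed ANOVA will be used to assesses the effects of cueing modality and walk order on outcomes", namely cadence, gait speed, stride length and the coefficient of variation (CV) of stride time. In that model "cueing modality will be modelled as a within-subject factor, while walk order as a between-subject factor to account for potential sequence effects".
- **Check.** "residual normality and normality of gait characteristics within each cue condition will be assessed using the Shapiro-Wilk test". No level is given for Shapiro–Wilk, and the section does not say whether one failed check is enough.
- **Switch.** "If assumptions for normality are not met, a Friedman test will be used to assess within-subject differences across cueing conditions". After that, "Post-hoc Wilcoxon signed-rank tests, with Bonferroni correction, will be conducted only if the Friedman test is statistically significant". No such condition is stated for the paired t-tests of the parametric route.
- **Walk order after the switch.** A Kruskal–Wallis "test will be used to assess group-level differences between walk-order groups". For interaction, "Interaction effects between cueing and walk order will be explored non-parametrically by conducting separate Friedman tests within each walk order group".
- **Status.** Comparisons of one cue with another are listed among the secondary and exploratory analyses, for which a two-sided p-value "of 0.05 will be considered statistically significant across all parametric and nonparametric tests".

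Under Walking/gait tasks, the three sequences of 20 order the cued walks as metronome–instrumental–vocal, instrumental–vocal–metronome and vocal–metronome–instrumental.

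**The concern.** Two things are fixed badly.

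First, the data choose the analysis separately for each of four outcomes. One outcome may be reported from a joint model with Cohen's d, and the next from rank tests with r = Z/√N and a different condition for post-hoc testing. The Discussion puts its emphasis on effect sizes and on consistency of response, and a mix of methods works against that.

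Second, the rank route does not replace what it removes. The mixed ANOVA estimates cue, sequence and their interaction together. In this three-sequence design, the interaction term also absorbs differences due to walk position (fatigue, practice, adaptation). The pooled Friedman test leaves those differences in the noise. The separate within-sequence tests mix them with the cue effect, and they can be read as evidence about interaction when they carry none. The Discussion says responses will be interpreted in the light of cue order and adaptation over time, so this is information the trial intends to use.

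**Working it through.** The plan gives no figure for the normality gate or the rank route, so there is nothing of its own to reproduce here.

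**1. What a within-sequence Friedman test can see**

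| | First cued walk | Second | Third |
|---|---|---|---|
| Sequence 1 | Metronome | Instrumental | Vocal |
| Sequence 2 | Instrumental | Vocal | Metronome |
| Sequence 3 | Vocal | Metronome | Instrumental |

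Within a row, each cue occurs at exactly one position. A difference between cues and a difference between positions therefore look the same. An interaction is a difference between rows, and three separate row-wise tests never make that comparison.

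**2. How these tests behave (simulation)**

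Inputs from the plan: three cues, three sequences, and 60 recruited less 10% attrition, so 60 × 0.9 = 54, or 18 per sequence. Assumptions: normal data, within-person correlation 0.5, test level 0.05, and a drift of 0.5 SD from first to third cued walk.

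- *Drift only, no cue effect.* Each within-sequence Friedman test is significant about 31% of the time. The sequences contain different people, so the chance of at least one is 1 − (1 − 0.31)³ = 1 − 0.329 = 0.67. The mixed-ANOVA cue test stays near 5%.
- *Cue effect only, no drift and no interaction.* With a largest cue-to-cue standardised response mean (SRM) of 0.5 and 20 people, one such test rejects 37% of the time. A rejection here reflects the cue, not an interaction.

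So these tests reject for drift alone and for cue alone, and they do not separate either from an interaction.

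**3. Pooled Friedman test against mixed ANOVA**

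At correlation 0.5 the SD of a cue-to-cue difference is √(2 × (1 − 0.5)) = 1, so an SRM of 0.5 is a 0.5 SD shift. Cue means are equally spaced and the level is 0.05.

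| Setting | Mixed ANOVA | Friedman |
|---|---|---|
| No drift, 55 participants | 92.0% | 80.1% |
| 0.5 SD drift, 54 participants | about 91% | about 75% |

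The no-drift gap agrees with theory. The asymptotic relative efficiency of Friedman under normality is (3/π) × k/(k + 1), which for k = 3 is 0.955 × 0.75 = 0.716. Thus 55 people act like 55 × 0.716 ≈ 39. The pairwise loss is much smaller: paired t against Wilcoxon is 95.5% against 94.7% at level 0.05, and 73.0% against 69.4% at 0.0033.

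**4. How often the gate opens by chance**

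With exactly normal data and Shapiro–Wilk at an assumed 0.05:

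- If any failure among three cue checks and a pooled residual check is enough, about 17% of outcomes switch (15–18% over correlations up to 0.9). The bound for four independent tests is 1 − 0.95⁴ = 0.185.
- If only the residual check decides, about 3–4% switch.
- With the three cue checks alone, at least one of four outcomes switches in 44–47% of trials, over between-outcome correlations from 0 to 0.6.

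**5. Average cost of the gate**

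The plan switches only some of the time, so the cost is roughly the switch rate times the gap: 0.17 × (92.0 − 80.1) ≈ 2.0 points without drift, and 0.17 × (91 − 75) ≈ 2.7 points with it. Direct simulation of the gated procedure (55 participants, cue shifts of 0, 0.15 and 0.35 SD, no drift) agrees: 63.6% falls to 61.1% at correlation 0.5, and 84.7% to 82.8% at 0.7. With no cue effect, the gated test rejects 5.4% of the time against 5.4% for ANOVA alone (correlation 0.5), and 4.9% against 4.8% (correlation 0.7).

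**The case against.** A fallback from ANOVA to rank tests is conventional and is written down in advance. Its average cost under normality is about 2–3 points, and no type I inflation was seen. The level and the rule for combining checks may be in an analysis plan that is not shown. The analyses mainly affected are secondary, and the Discussion plays down formal testing. All of this stands, and it limits how serious the point is.

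Four stronger readings are tempting, but the document does not support them:

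- *Chance will often move an outcome to the rank route.* This needs both a 0.05 level and an any-failure rule, and neither is stated. If residuals alone decide, switching is rare.
- *The plan loses 12 or more points of power.* That compares always using ANOVA with always using Friedman. The plan does neither.
- *Walk order is dropped.* Kruskal–Wallis still compares the walk-order groups. What is lost is the joint model.
- *The normality check is aimed at the wrong quantity.* Residuals are checked as well. The within-condition check can be read as a check on each cue's change from baseline, which suits a paired comparison with the uncued walk.

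The objection does not rescue the within-sequence Friedman tests. They are specified for a question they cannot answer, however rarely the gate opens. Nor is a switch always a matter of chance: with mildly skewed data (lognormal, sigma 0.2), at least one of three cue checks fails 69% of the time. The rank route may then be the usual one for such an outcome.

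**Conclusion.** The point holds in limited form. Normality tests choose the analysis for each outcome. When they choose the rank route, the joint model of cue, walk order and interaction is lost, and what stands in for the interaction confounds cue with walk position. Under an assumed 0.5 SD drift and no cue effect, each of those tests is significant about 31% of the time and at least one in about 67%. The pooled Friedman test has about 75% power where the mixed ANOVA has 91%. These figures rest on normal data, 54 participants, within-person correlation 0.5 and a drift size that the document does not give.

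The gate's average cost under normality is small, and error inflation should not be claimed. Type I error under the gate was not examined for skewed data. The document does not name the test for the three primary comparisons, so the effect on the primary claim cannot be determined. The change is worth making, but the main result does not depend on it.

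**What to change.** Name one model for every outcome, to be used whatever Shapiro–Wilk shows. Either of these would do:

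- the planned mixed ANOVA with cue, sequence and their interaction; or
- a linear mixed model with cue and walk position as fixed effects and a random participant effect, with a statement that walk position stands in for the cue-by-sequence term.

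Keep the log-ratio scale for the CV of stride time. Judge residuals by Q–Q plot. Report Friedman and Wilcoxon results for every outcome as sensitivity analyses, not only when a normality check fails. Delete the separate within-sequence Friedman tests as a test of interaction.

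The cost is a few sentences of analysis wording and one sensitivity table. The downside is reliance on moderate-sample robustness if residuals are badly skewed. The sensitivity table would show where that matters.
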